## Abstract

**Background:**

Gastrointestinal dysfunction is one of the common complaints for patient post-surgery. Acupuncture has been employed to improve gastrointestinal function and sleeping quality and has confirmed clinical efficacy for emotional problems. This study aims to evaluate the clinical effect of electroacupuncture for postoperative rapid recovery.

**Methods:**

This study design is a two-arm, parallel, double-blinded randomized controlled trial. 104 subjects, aged from 40 to 89 years old, diagnosed with gastrointestinal cancer undergoing laparoscopic surgery, will be divided into Interventional Group and Control Group. Patients of both groups receive perioperative care under the guidance of ERAS guidance. The Interventional Group receives electroacupuncture treatment starting from the first day post-surgery for a consecutive 5 days, whereas the Control Group receives placebo electroacupuncture treatment. The primary outcome will be the first flatus time whereas the secondary outcomes will be the first sign of borborygmus, recovery of defecation, laboratory tests and questionnaires including Self-rating anxiety scale, Ford Insomnia Response to Stress Test, TCM rating scale of Gastrointestinal symptoms and Gastrointestinal Symptoms Rating Scales.

**Discussion:**

This study aims to provide timely intervention for post-laparoscopic patients with gastrointestinal tumour using the ERAS concept combined with electroacupuncture, observe the efficacy of this therapy in treating PGID, and contribute reliable scientific evidence for postoperative rapid recovery.

**Trial registration:**

Chictr.org.cn Identifier: ChiCTR2300078710. Registered on 15th December 2023.

**Supplementary Information:**

The online version contains supplementary material available at 10.1186/s12906-024-04418-0.

## Introduction

According to the Global Cancer Statistics for 2020, colorectal cancer is ranked as the third most commonly diagnosed cancer, and gastric cancer holds the fifth position. The morbidity and mortality rates for both have been steadily increasing, highlighting the substantial global burden they impose [1]. Thus far, surgical intervention remains the predominant solution for cancers in their early stages or without metastasis. While among surgical plans, laparoscopic surgery has the advantages of less trauma and faster recovery [2], which has gradually taken over traditional open surgery. However, the effect of both surgical plans remains controversial due to several factors. A meta-analysis related to the effect of complications of laparoscopic versus open surgery showed that there is no significant difference between both surgical plans in terms of infection [3]. In fact, laparoscopic surgery may still lead to post-surgery complications ranging from prolonged ileus, constipation to vomiting and nausea due to the usage of intraoperative anaesthesia drugs, carbon dioxide insufflation, etc [4].

The ERAS concept aims to improve the quality of life for patients by alleviating perioperative stress responses, reducing postoperative complications, shortening hospital stays, and relieving negative emotions. Its clinical pathway spans the entire diagnostic and treatment process, including pre-hospitalization, preoperative, intraoperative, postoperative, and post-discharge phases [5]. Based on previous studies, the adoption of the ERAS concept can significantly enhance the efficiency of surgical patient care, accelerate patient recovery, and improve postoperative quality of life [6–8]. In recent years, exploring other adjuvant treatment measures has become a hot topic and focus in clinical research. Many clinicians have actively incorporated acupuncture and electroacupuncture therapy based on the ERAS concept, aiming to achieve better therapeutic effects in promoting post-gastrointestinal surgery recovery. However, the use of the Eight Confluent Points remains a blank area in the rapid recovery after laparoscopic surgery for gastrointestinal tumours, representing an innovative approach both domestically and internationally.

A research progress on the molecular mechanism showed that electroacupuncture may relieve gastrointestinal mucosal damage and adjust gastrointestinal motility disorders via modulating the central and peripheral nerve signalling [9], while a study by [name] team has proved the distal effect of acupuncture [10, 11]. Apart from that, inflammatory cytokines could predict and reflect the infectious complications of colorectal surgery where acupuncture therapy is likewise proved to be able to down-regulate serum levels of relative inflammatory factors of patients with cancer-related fatigue [12, 13]. Electroacupuncture as a TCM therapy, has improving effects on gastrointestinal dysfunction [14–16]. Among the clinical trials, acupoints Zusanli (ST 36), Tianshu (ST25), and Shangjuxu (ST 37) are frequently used. Therefore, the therapeutic role of electroacupuncture accelerating post-surgery gastrointestinal recovery using the Eight Confluent Points is elucidated in this trial, aiming to provide evidence for clinical use.

This study aims to provide timely intervention for post-laparoscopic patients with gastrointestinal tumour using the ERAS concept combined with electroacupuncture, observe the efficacy of this therapy in treating PGID.

## Materials and methods

### Study design

This study design is a two-arm, parallel, double-blinded randomized controlled trial aimed to study the effectiveness of electroacupuncture for improving the first flatus time of post-surgery patients. The study protocol followed the SPIRIT guidelines [17].

### Participants

#### Recruitment strategies

Participants will be recruited from the inpatient department of Gastrointestinal Surgery, Shanghai Seventh People’s Hospital. Recruitment posters will be distributed at the outpatient departments. Participants are considered for inclusion if they meet the criteria as follows.

#### Inclusion criteria

Patients eligible for the study must comply with the following criteria:

Diagnosed as primary gastrointestinal tumours including gastric, colon and rectal tumours; Undergoing laparoscopic surgery performed by the surgeons of the Gastrointestinal Surgery Department, Shanghai Seventh People’s Hospital;TNM staging, Stage I-III;Aged 40–89 years old (including 40 and 89 years old);Consent to the participation of this study and is able to sign the informed consent form.

#### Exclusion criteria

Participants meeting any of the following criteria will be excluded:

Secondary gastrointestinal tumours;Patients with cognitive dysfunction, unable to understand or fill assessment forms;Pregnancy or lactation;Severe illness with gastrointestinal system before surgery; Severe heart, lung, liver, kidney, brain or systemic immune diseases;Allergic or intolerant to acupuncture.

#### Elimination criteria

Participants would be eliminated if they were found not meeting the inclusion criteria during the treatment period or statistical period.

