#### Dropout criteria

Participants with poor adherence;Participants fail to complete therapy within the requirement period;Participants request to leave the study for any reason.

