### Sample size

This randomized controlled trial aims to explore the improvement in the first flatus time of post-surgery patients on electroacupuncture therapy compared to placebo therapy. Based on a previous study conducted in China [18], sample size was calculated with 80% power and two-tailed α = 0.05, β = 0.20, taking the ratio of 1:1 for the interventional group and control group. Assuming a dropout rate of 15%, this study requires 52 subjects in each group, with a total of 104 subjects to be recruited.

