### Procedure

Participants will be assessed for eligibility by the doctors and nurses from the Gastrointestinal Surgery department before surgery. Participants who meet the criteria will be obtained informed consent. Then, the participants will undergo randomization and allocation before being enrolled in the treatment. Assessments and laboratory tests will be made according to the timeline (Fig. 1).

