### Statistical analyses

Data is analysed on the intention-to-treat (ITT) principle using all randomized participants. SPSS 25.0 is used to analyse data, with the statistical significance set at *P* < 0.05. Normally distributed continuous variables will be represented by mean and standard deviation (‾*x ± s*), and will be analysed using independent-samples *t*-test, whereas comparison of data within groups is done through paired *t*-test. Continuous variables that do not follow a normal distribution will be represented by median (quartiles), and will be analysed using the non-parametric test. Enumeration data will be analysed using the χ2 test. Categorical variables are analysed using a rank-sum test. Repeated measure ANOVA test will be used for statistical data recorded at multiple time points.

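### Eliminating randomised participants found ineligible, even at the analysis stage, contradicts the stated intention-to-treat analysis of everyone randomised

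*Protocol article*

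**What the plan says.** Four places in the protocol article bear on who enters the primary comparison.

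- Elimination criteria: "Participants would be eliminated if they were found not meeting the inclusion criteria during the treatment period or statistical period".
- Statistical analyses: "Data is analysed on the intention-to-treat (ITT) principle using all randomized participants".
- Dropout criteria, a list with no statement on data handling: "Participants with poor adherence;Participants fail to complete therapy within the requirement period;Participants request to leave the study for any reason".
- Sample size: "Assuming a dropout rate of 15%, this study requires 52 subjects in each group, with a total of 104 subjects to be recruited".

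The order of events is in the Procedure section. Eligibility is assessed before surgery and consent is taken. "Then, the participants will undergo randomization and allocation before being enrolled in the treatment".

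**The concern.** An elimination rule that runs through treatment and into the statistical work acts on people who already hold an allocation. At the statistical stage the outcomes exist, so elimination can hardly mean anything except removal from the dataset. The analysis section promises the opposite.

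At stake is the composition of the primary analysis set. If the conflict is left open, someone must choose between the two rules once first flatus times are in hand, case by case or for the whole trial. Exclusion that is related to recovery and unbalanced between arms could create an apparent benefit or hide a real one.

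**Working it through.** **1. The two rules applied to one participant.** Take a patient who is randomised, treated and has a first flatus time recorded, and who is found during data review to lie outside TNM stage I–III. Under the Elimination criteria this patient is removed. Under Statistical analyses this patient is included. No other section says which rule prevails, or that eliminated participants stay in the intention-to-treat set.

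**2. Which inclusion criteria can fail late.** The list covers tumour type, laparoscopic operation by the department's surgeons, TNM stage, age and consent. Age and consent are known at entry. Operative approach and stage may be confirmed or overturned only at or after surgery. Both could plausibly go with bowel recovery; a conversion to open surgery is one example. The rule names no decision-maker and does not require blinding to arm or outcome.

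**3. The dropout allowance.** The stated design inputs are these: "sample size was calculated with 80% power and two-tailed α = 0.05, β = 0.20, taking the ratio of 1:1". The article gives no effect size or standard deviation, so the full sample size cannot be reproduced. Only the inflation step can be checked: 44 / (1 − 0.15) = 51.8, rounded up to 52, which agrees with 52 per group. In reverse, 52 × 0.85 = 44.2. This fits planning on about 44 evaluable per arm, but it does not show whether the other 8 are expected to have missing outcomes or to be deleted.

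**4. Precision if removal is unrelated to arm and outcome.** On a two-sample normal approximation, 44 per arm has 80% power for a standardised difference of (1.960 + 0.842) × √(2/44) = 0.597. This is back-calculated and not stated in the article. With 52 per arm the same difference has power Φ(0.597 × √26 − 1.960) = 86%. Random removal therefore costs precision only.

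**5. An illustration of bias.** Taken from the article: 52 per arm and a two-sided 5% test. Assumed: no true effect, log-normal flatus times with median 48 h and log-SD 0.5, a Mann-Whitney test on those retained, and the exclusion rates and direction in the table. At 15% v 5% the excluded numbers are 0.15 × 52 = 7.8 (8) and 0.05 × 52 = 2.6 (3). Differences are electroacupuncture minus placebo.

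| Excluded (electroacupuncture v placebo) | Drawn from | Spurious difference | Type I error |
|---|---|---|---|
| 15% v 5% | slower half | −2.4 to −2.6 h | 6.7 to 8.4% |
| 15% v 5% | faster half | +2.6 h | 7.1% |
| 15% v 5% | unrelated to outcome | −0.1 h | 5.1% |
| 15% v 15% | slower half | 0.0 h | 4.2 to 5.9% |

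The lower error rates in each range come from fixing the number excluded; the higher ones arise when that number varies by chance around the rate. A harsher assumption (normal outcome, t-test, the very slowest removed) gives 17% and a shift of 0.16 SD for the same 15% v 5% split.

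**The case against.** **Elimination concerns eligibility, not treatment response.** The rule covers the inclusion criteria only. Apart from consent, these are facts of the patient or the operation, and treatment starts the day after surgery, so the assigned arm cannot change them. This stands in good part. Removal for such facts, judged blind, would carry little bias. But the rule does not set that condition, and it still contradicts the analysis statement.

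**The people handling the data are blinded.** The Blinding section withholds allocation from data collectors and statisticians. This lowers the risk of arm-aware removal. It does not settle the point: the article does not say who decides on elimination, the acupuncturists know the allocation, and being blind to arm is not being blind to outcome.

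**Dropouts and the 15% allowance.** A reader might infer that people with poor adherence or incomplete therapy are deleted, so that the analysis becomes one of completers, with losses driven by the arms' different needling and current. The documents do not support that. The Dropout criteria only say who counts as a dropout, and intention-to-treat analysis exists for such people. Inflating for dropout is routine under it, to cover missing outcomes. Many dropouts may also have the outcome already: under the assumed distribution, ln(120/48)/0.5 = 1.83, so about 97% would pass flatus within 120 h.

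**The simulated bias depends on its assumptions.** This stands. The sign reverses if fast recoverers are removed, and the bias vanishes if removal is unrelated to outcome.

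**A statistical analysis plan may fill the gap.** That would answer an absent definition of a per-protocol set, which is no fault here. It does not answer two rules that are both stated and disagree.

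**Conclusion.** Wrong as written: an internal contradiction. It rests on the text alone and needs no numerical assumption. The Elimination criteria remove randomised participants as late as the analysis stage, while the Statistical analyses section keeps everyone randomised.

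The consequence is exposure to selective exclusion in the primary comparison, not a demonstrated bias. The documents give no exclusion rates by arm and no link between exclusion and recovery, so its size cannot be derived. The figure of about 7 to 8% type I error holds only under an assumed 15% v 5% exclusion of slower recoverers. There is no bias if exclusion is unrelated to arm or outcome.

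For dropouts the finding is limited to an ambiguity that should be aligned with the analysis statement.

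**What to change.** 1. In the Elimination criteria, delete the statistical period as a ground for removal.
2. In Statistical analyses, state that every randomised participant stays in the primary intention-to-treat analysis in the assigned arm, including those eliminated or classed as dropouts.
3. State that first flatus time continues to be recorded for these participants where they agree.
4. Use late-found ineligibility, poor adherence and incomplete therapy only to define a per-protocol sensitivity analysis, with classification by people blind to arm and outcome.

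These changes concern the analysis set and data collection; they leave clinical handling as it is. The cost is a wording amendment by the route in the Protocol amendments section, plus continued recording of an outcome already collected on the ward. No extra patients are needed. The amendment should be in place before any outcome data are analysed (the article plans analysis from July 2026), so that the choice between the two rules cannot be made knowing the result.

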#### Dropout criteria

Participants with poor adherence;Participants fail to complete therapy within the requirement period;Participants request to leave the study for any reason.

#### Discontinuation criteria

Participants request to leave the study;Severe complications or infection occur post-surgery, in which the patient is to be transferred to another department for further specialized treatment;Severe allergy or adverse events occur during the interventional period.

### Sample size

This randomized controlled trial aims to explore the improvement in the first flatus time of post-surgery patients on electroacupuncture therapy compared to placebo therapy. Based on a previous study conducted in China [18], sample size was calculated with 80% power and two-tailed α = 0.05, β = 0.20, taking the ratio of 1:1 for the interventional group and control group. Assuming a dropout rate of 15%, this study requires 52 subjects in each group, with a total of 104 subjects to be recruited.

### Ethics and trial registration

Ethics for this study protocol and informed consent materials have been approved by the Ethics Committee of Shanghai Seventh People’s Hospital affiliated to Shanghai University of Traditional Chinese Medicine on 5th December 2023, with committee approval number: 2023-7th-HIRB-078. This study has likewise been registered at Chinese Clinical Trial Registry, with approval number: ChiCTR2300078710.

### Procedure

Participants will be assessed for eligibility by the doctors and nurses from the Gastrointestinal Surgery department before surgery. Participants who meet the criteria will be obtained informed consent. Then, the participants will undergo randomization and allocation before being enrolled in the treatment. Assessments and laboratory tests will be made according to the timeline (Fig. 1).

**Fig. 1 Fig1:**
[figure not shown]
CONSORT flow diagram of study design

After the intervention period, the participants will receive postoperative care according to the guidelines of the Gastrointestinal Surgery department until they are discharged from hospital. Participants in the CG group will be invited to receive 5 acupuncture treatments free of charge on voluntary basis as post-trial care.

Follow-ups will be done on the first month and third month after the surgery.

### Randomization

The experiment adopts a simple randomization method for grouping, wherein a random number table is generated using SPSS 25.0 software. The random allocation cards are sealed in opaque envelopes and kept by designated personnel of the research team. When eligible subjects agree to participate in the trial, envelopes are assigned based on the order of patient visits. Only at this point can the envelope be opened, and the subjects are then enrolled in the treatment according to the assigned group.

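### Simple randomisation does not guarantee the stated 52 per group and leaves the balance of gastric, colon and rectal operations to chance; blocks stratified by site would be a cheap improvement

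*Protocol article*

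**What the plan says.** All places are in the protocol article.

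- **Randomization:** "The experiment adopts a simple randomization method for grouping, wherein a random number table is generated using SPSS 25.0 software". Allocation cards are kept in sealed opaque envelopes, and "envelopes are assigned based on the order of patient visits". No block, stratum or minimisation factor is named.
- **Sample size:** "sample size was calculated with 80% power and two-tailed α = 0.05, β = 0.20", "taking the ratio of 1:1 for the interventional group and control group". With 15% dropout, "this study requires 52 subjects in each group, with a total of 104 subjects to be recruited". Neither the effect size nor the standard deviation (SD) is printed.
- **Inclusion criteria:** "Diagnosed as primary gastrointestinal tumours including gastric, colon and rectal tumours". The expected share of each site is not given.
- **Primary outcome:** time from return to the ward until first flatus.
- **Statistical analyses:** an independent-samples t-test for normal continuous data and a non-parametric test otherwise. No covariate or stratification factor is named.
- **Trial status:** no participant had been recruited when the article was submitted.

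**The concern.** Two statements do not fit together. The sample size is expressed as a fixed number in each arm, but simple randomisation fixes neither arm's size.

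In addition, the trial pools operations on different parts of the gut and measures a bowel-function endpoint. Tumour site may well be related to time to first flatus, and it is established at eligibility assessment before surgery, so it is available at allocation without extra work. The stated method does not use it, and the listed tests do not mention it. In a trial of 104 patients, a chance excess of one type of operation in one arm could move the observed difference. Any outcome variance that site explains would stay in the error term.

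**Working it through.** **1. The plan's own figure.** The formula is n per arm = 2(1.960 + 0.842)² / d², with d the standardised difference. As no d is printed, 52 can only be solved backwards.

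- 44 / 0.85 = 51.8, rounded up to 52 (45 × 1.15 = 51.75 also rounds up to 52).
- d = 2.802 × √(2/44) = 0.597; with 45 per arm it is 0.591.

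So 52 per group is consistent with d of about 0.60 but cannot be verified from the article. I use d = 0.597, which gives 80% power at 44 evaluable patients per arm.

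**2. Arm sizes under simple randomisation.** The number in one arm is Binomial(104, 0.5), with mean 52 and SD √(104 × 0.25) = 5.1.

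- Exactly 52/52: 7.8%.
- 95% range for one arm: 42 to 62 (52 ± 1.96 × 5.1).
- Arms differ by 10 or more (smaller arm 47 or fewer): 38%.
- Smaller arm 44 or fewer: 14%.

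**3. What unequal arms cost.** Scale each arm by 44/52 for dropout. Power = Φ(d / √(1/n₁ + 1/n₂) − 1.960).

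| Randomised split | Power |
|---|---|
| 52/52 | 80.0% |
| 46/58 | 79.5% |
| 44/60 | 79.1% |
| 42/62 | 78.5% |
| Average over the binomial | 79.6% |

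At 42/62, for example, n₁ = 35.5 and n₂ = 52.5, and the statistic is 0.597 / 0.2173 − 1.960 = 0.789, so power is 78.5%.

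**4. Balance of tumour site.** The share of one site is assumed to be 20%, 30%, 40% or 50%. The SD of the between-arm difference in that share is about √(4p(1 − p)/104). The probabilities come from 200,000 simulated trials per row.

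| Assumed share p | SD (points) | ≥10 points | ≥15 points | ≥20 points |
|---|---|---|---|---|
| 20% | 7.9 | 20% | 6% | 1% |
| 30% | 9.0 | 27% | 10% | 3% |
| 40% | 9.6 | 30% | 12% | 4% |
| 50% | 9.9 | 30% | 13% | 4% |

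**5. What an imbalance could do.** Assume that site shifts the outcome by s = 0.3 to 1.0 within-site SDs, and let v = p(1 − p)s². A 15-point imbalance moves the unadjusted difference by 0.15s / √(1 + v), in total-SD units. That is about 0.045 at s = 0.3 and up to 0.139 at s = 1.0, or 8% to 23% of d = 0.597.

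**6. What adjustment would gain.** Site explains R² = v / (1 + v) of the variance, and adjusted power = Φ(2.802 / √(1 − R²) − 1.960).

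- Weakest case (p = 20%, s = 0.3): R² = 0.014, power 80.6%.
- Strongest case (p = 50%, s = 1.0): R² = 0.20, power 87.9%.

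Power therefore rises from 80% to about 81-88% at the same sample size.

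**The case against.** Simple randomisation is a valid method, and much of the case against this point stands.

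- A reader might infer that tumour site will be unbalanced, or that the test will be biased. The article does not support that. Simple randomisation balances site in expectation, and the unadjusted test keeps its type I error because chance imbalance is already part of its sampling variance.
- A reader might infer that a smaller arm of 44 before dropout seriously damages power. It does not: when one arm has 44 the other has 60, and power is 79.1%.
- The term may be loose wording for a shuffled set of 52 + 52 cards, which would end at exactly 52/52. The article does not say so. If that is what was done, the binomial figures in step 2 do not apply and the description needs correcting.
- Covariates are commonly left to a statistical analysis plan, which is not shown. It can be said that the article's listed tests name none, but not that the primary analysis will ignore site.
- The Discussion mentions a risk of confounding, but ties it to the single-centre design and restricted sample. It is no admission about allocation or tumour site.
- The site mix and the strength of its effect on flatus time are not in the article. With a weak effect, the gain from adjustment is about 1 point of power.

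Two things survive. The stated method does not secure the stated arm sizes. A separate analysis plan could add adjustment, but it could not supply stratified allocation where the protocol specifies simple randomisation.

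**Conclusion.** The point holds as a worthwhile and inexpensive improvement, not as a failure of validity. The arm-size mismatch is a matter of internal consistency with little effect on power: about 0.4 points on average and under 2 points at 42/62. The stronger reason to act is that a plausible prognostic factor, known before allocation, is left to chance. An imbalance of 15 points or more in its share has a 6-13% probability and could shift the unadjusted difference by 8-23% of the implied effect.

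The binomial results rest only on the stated total and on taking simple randomisation literally. The site results rest on an assumed share of 20-50% and an assumed shift of 0.3-1.0 SD. The implied d of about 0.60 is back-solved.

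**What to change.** - Replace simple randomisation with 1:1 permuted blocks of concealed, randomly varying size, stratified by tumour site (gastric / colorectal, or gastric / colon / rectal). Keep the same sealed opaque envelopes, one series per stratum, with the list generated by someone outside recruitment. This holds the arms at or near 52/52.
- Include site in the primary analysis, so that the analysis matches the allocation and gains the precision.
- If recruitment has begun, prespecify adjustment for site before unblinding. This still secures the analysis part of the benefit.
- If the existing list is a shuffled set of 52 + 52 cards, say so and stop calling it simple randomisation.

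The cost is a new list and one model term. The downside is slight predictability at block ends for the acupuncturists, who are not blinded. Varying block sizes limit it, as does the existing arrangement in which appointed staff hold the envelopes.
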